### Intervention

The AE will be executed in a climate-controlled aquatic research laboratory, and the LE will be performed in a motion analysis laboratory. During AE, participants will stand barefoot on an adjustable floor of an aquatic treadmill (HydroWorx 2000TM, Middletown, PA), and the water depth will be adjusted to each participant’s xiphoid process level. Participants will sit on a chair for five minutes before AE for environmental acclimatization.

Participants will engage in a single bout intervention consisting of 120 repetitions of a ball throwing and catching task using a volleyball (Wilson Sporting Goods Co., Chicago, IL, USA). This single-session approach was selected based on a previous study, reporting the long-lasting effects of a single bout intervention with an intense reactive balance exercise [34]. Several previous studies also demonstrated that reactive balance in response to a postural perturbation has been improved after a single bout intervention [8,9,11–13].

The participants will be asked to throw the ball at a self-paced high speed at the chest-to-shoulder level using two hands towards the trainer’s hands positioned at a 3-meter distance from them and 20-degree above an imaginary horizontal line at each participant’s eye level. For the consistent height and trajectory of the ball across all sessions, the trainer will kneel on the floor in front of the pool during AE sessions and stand on a step box during LE sessions. Then, they will catch the ball thrown at a moderate speed by the trainer directly toward the midline of their body, to the left or right of the midline, or to the closer or farther point from the trainer to induce fixed-support reactions and change-in-support reactions in both frontal and sagittal planes of the participants. The directions of the ball will be random and unpredictable, and the number of the directions will be proportionately included. After each repetition involving one throw and one catch, participants will be asked to return to the start position for the next repetition. The intervention session will be composed of 3 sets of 40 repetitions with a 2-min break after the first and second set. Of the 120 repetitions, the catches will follow 60 direct throws and 60 deceptive throws from the trainer to introduce the concepts of response inhibition and action selection. For example, a deceptive throw will involve a deceptive action that provides misleading information about the direction of the ball projection (e.g., a throwing motion to the right without an actual throw) before the actual throw (e.g., throwing the ball to the left, which is the predetermined direction). While catching the ball, the participants will be allowed to select whichever strategy they wish and freely move their bodies to properly react and catch the ball. The Borg Scale for Rating of Perceived Exertion (RPE) will be used during each intervention set, and the heart rate will be recorded using a finger pulse oximeter (SportStat; Nonin Medical, Inc., Minneapolis, MN. USA) before and after each set to subjectively and objectively monitor the intensity of the exercise. Additional rest will be given if needed. The exercise intervention procedures used previously in several trials have been reproduced and modified to generate reliable results in accordance with our research purpose [9,11–13]. After each intervention session, subjective measures of satisfaction, difficulty, and safety levels will be additionally performed using a visual analogue scale (VAS, range: 1–10).

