## Abstract

Reactive balance, a critical automatic movement pattern in response to a perturbation, is directly linked to fall prevention in older adults. Various exercise interventions have been broadly performed to improve reactive balance and thus prevent falls. Curiously, aquatic exercises have been suggested as an effective balance intervention and a safer alternative to exercises on dry land yet the efficacy of aquatic exercises on reactive balance has not been formally investigated. The present clinical trial aims to identify if skills acquired during aquatic exercise are more effectively transferred to a reactive balance task than land exercise. This study is designed as a double-blinded, randomized controlled clinical trial. Forty-four older adults aged 65 years or above who meet the eligibility criteria will be recruited and randomized into an aquatic exercise group or land exercise group. Each group will participate in the same single bout intervention that includes a ball throwing and catching task. A modified lean-and-release test will be implemented on land immediately before, after, and one week after the single bout intervention. The outcomes will include reaction time, rapid response accuracy, and mini-BESTest scores obtained from stepping and grasping reactions. All statistical analyses will be conducted using an intention-to-treat approach. Our conceptual hypothesis is that participants in the aquatic exercise group will demonstrate more improved outcome scores in the lean-and-release test when compared to those in the land exercise group. The results of the present study are expected to provide evidence to support the benefits of aquatic exercises for improving reactive balance in older adults. Further, participants may find aquatic exercises safer and more motivating, thus encouraging them to participate in further aquatic exercise programs.

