
### Outcome measurement

A modified lean-and-release technique devised by Bolton and Mansour (2020) will be implemented on land to assess reactive balance immediately before (pre), after (post), and one week after (follow-up) the single bout intervention [25]. Lean-and-release techniques are commonly used to assess reactive balance in various older adult populations [35–37]. This modified lean-and-release technique additionally introduces cognitive factors (i.e., response inhibition and action selection), which are important in certain situations. For safety purposes, participants will wear a harness, which is secured to the ceiling to prevent them from falling in case they fail to recover balance. The participants will then stand with both feet hip-width apart on two separate, parallel force plates (type 9260AA, Kistler AG, Winterthur, Switzerland). A horizontal cable will be attached to the safety harness at the midthoracic level and the other end to the wall behind the participants by a magnet. To simulate a forward fall (trip) situation, the experimenter will instruct participants to lean forward into a support cable while keeping both feet in contact with the floor and to remain relaxed (Fig 2). This position will require dorsiflexion of the ankle, as the rest of the body remains aligned. The forward lean position for each participant, measured by the ankle joint angle, will be determined as the minimal lean angle where a change-of-support reaction (i.e., forward step) is necessary to recover balance upon cable release [38]. Then, the magnet will be deactivated to suddenly release the cable. There are two possible settings: 1) the leg block is placed in front of both legs, and a safety handle is uncovered; or 2) the leg block is removed, and the safety handle is covered. The leg block and handle cover will be controlled via computer-triggered, servo motors. The testing session will be comprised of three blocks: 1) REACH (grasping a safety handle using their right hand while maintaining both feet fixed), 2) STEP (stepping forward using any leg), and 3) RANDOM (random variations of STEP and REACH). To control vision during the third block, participants will wear liquid crystal goggles (Translucent Technologies Inc. Toronto, ON, Canada), that will be closed at the beginning of each trial and opened 400 ms before the cable is released. An experimenter will make careful note of the stepping leg used on each trial, and the participants will be free to step with either leg during testing. The timing of foot-off of the stepping foot will be recorded using the two parallel force plates. A force-sensitive resistor (B&L Engineering, Santa Ana, CA, USA) placed on the top surface of the safety handle and one large force plate in front of the two parallel force plates will be used to detect hand contact with the safety handle during REACH and foot contact during STEP, respectively. To control the predictability of the forthcoming reactions during the third block, the settings will be randomly changed between trials via the data collection program. After sufficient practice trials to familiarize the participants with the stepping and reaching actions, five trials each of the REACH and STEP will be completed, and ten actual trials of RANDOM, including five STEP and five REACH actions in random orders, will be completed. Outcome measurements at post and follow-up will include all randomized participants within the original groups regardless of any discontinuation or deviation from intervention protocols.

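### The post-test follows exercise immediately in both arms, but only AE participants must leave the water first, so the exercise-to-test interval probably differs by arm and is neither equalised nor recorded

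*Protocol article*

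**What the plan says.** Under Intervention, the article separates the two settings: "The AE will be executed in a climate-controlled aquatic research laboratory, and the LE will be performed in a motion analysis laboratory". For AE, "the water depth will be adjusted to each participant’s xiphoid process level", and participants stand barefoot. The same section gives AE a preparatory wait: "Participants will sit on a chair for five minutes before AE for environmental acclimatization". No counterpart is stated for LE.

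The exercise dose is common to both arms: "The intervention session will be composed of 3 sets of 40 repetitions with a 2-min break after the first and second set". There is also a discretionary element: "Additional rest will be given if needed". Perceived exertion is rated during each set and heart rate is taken before and after each set. Neither is stated to be taken at the start of the post-test. Visual analogue ratings follow each session in both arms.

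Under Outcome measurement, the lean-and-release test "will be implemented on land to assess reactive balance immediately before (pre), after (post), and one week after (follow-up) the single bout intervention". This wording applies to both arms. No minutes are given and the test room is not named. The Abstract describes the arms as otherwise alike: "Each group will participate in the same single bout intervention". Under Statistical analysis, the planned model is a group-by-time repeated-measures ANOVA with three time points. The exercise-to-test interval does not appear in it.

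**The concern.** The trial asks whether the exercise environment changes transfer to a land task. That requires the arms to differ in environment and, as far as possible, in nothing else when they are tested. A rule of testing immediately after exercise does not achieve this when one arm ends in the water and the other on land. Followed literally, it allows LE participants to be tested straight away and AE participants only once they are out of the pool and ready.

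Several outcomes are times in milliseconds, measured in adults aged 65 or above after 120 repetitions thrown at high speed. It is plausible that they respond to the participant's state in the minutes after exercise. If so, a group difference at the immediate post-test would mix environment with time since exercise. If the interval is not logged, this could not be examined afterwards.

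**Working it through.** **No plan figure to reproduce.** The article gives no interval and no expected effect of one. The check is a comparison of passages, followed by an illustration under assumed values.

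**1. Passages side by side**

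| Step | AE | LE | Source |
|---|---|---|---|
| Seated wait before exercise | 5 minutes | none stated | Intervention |
| Place of exercise | aquatic laboratory, xiphoid-deep water | motion analysis laboratory | Intervention |
| Exercise | 3 × 40 = 120 repetitions | same | Intervention |
| Ratings after the session | yes | yes | Intervention |
| Leaving the water | necessary | not applicable | follows from the settings |
| Place of test | on land, room not named | same | Outcome measurement |
| Time of post-test | immediately after | same | Outcome measurement |

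Leaving the water is the one step between exercise and post-test that necessarily applies to AE alone. Unless LE participants are made to wait, the same rule gives AE the longer interval. No such wait is stated.

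**2. What an unequal interval could do.** Two mechanisms act in opposite directions. Longer recovery from fatigue could improve AE performance. Longer fading of an acute practice or warm-up effect could worsen it. The article has no data on either, so the sign cannot be fixed.

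**3. Illustration of size.** Inputs from the article: alpha 0.05; 22 per group at entry; 19 per group required by the power calculation. Assumptions of this review: a two-sided test (the article does not state sidedness), no true environment effect, a two-sample t-test at the post-test alone, and a spurious shift of b SD caused only by the interval.

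Rejection probability = P(|T| > critical value), where T is noncentral t with 2n − 2 degrees of freedom and noncentrality b × √(n/2).

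- For n = 22, √(22/2) = 3.317, so the noncentrality is 0.33, 0.66, 1.00 and 1.66 for b = 0.1, 0.2, 0.3 and 0.5.
- For n = 19, √(19/2) = 3.082, so it is 0.31, 0.62, 0.92 and 1.54.

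| Assumed shift (SD) | n = 22 per group | n = 19 per group |
|---|---|---|
| 0.1 | 6.2% | 6.0% |
| 0.2 | 9.9% | 9.2% |
| 0.3 | 16.3% | 14.7% |
| 0.5 | 36.7% | 32.3% |

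No shift in this table comes from the article, and the test is simpler than the planned ANOVA. The table shows how sensitive a trial of this size would be; it does not estimate the bias.

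**4. The one-week time point.** A difference of minutes in recovery on the exercise day has no evident route to a test one week later. The follow-up comparison is therefore essentially free of this problem.

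**5. Before exercise.** The pre-test is also set as immediate in both arms, yet AE has five seated minutes before exercise. This lengthens the pre-test-to-exercise interval in AE only. It precedes the exercise, so it cannot itself change recovery afterwards.

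**The case against.** The strongest reply is that a journal article condenses, and that minutes between last set and test belong in an operating procedure. That would settle the matter if the point rested on silence. It rests on what is stated: one rule of immediacy for both arms, and settings under which that rule gives unequal intervals unless LE participants wait.

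Other parts of the reply stand:

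- **Drying, changing and a room change.** A reader might infer that only AE participants dry off and move to another room. The text mentions neither drying nor changing, and the test room is not named, so LE participants may also have to move. Only leaving the water follows from the text.
- **Fatigue and its direction.** A reader might infer that extra rest would shorten AE reaction times and favour the hypothesis. Breaks and extra rest are provided, monitoring exertion does not show fatigue at testing, and fading of a warm-up effect would work against AE.
- **Steps common to both arms.** The ratings and fitting of the harness and cable give LE participants some recovery too. They narrow the contrast in relative terms but do not remove the AE-only step.
- **Follow-up as a safeguard.** It would be too strong to say that nothing in the planned analysis can separate environment from recovery. A difference retained at one week could not readily be put down to minutes of rest; one seen only at the immediate post-test could.
- **The seated period.** It is described as acclimatization, and the shared bout can be read as the ball task alone. It is a difference in timing to tidy up, not a clear contradiction.

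**Conclusion.** The point holds in limited form. The exercise-to-test interval will probably be longer in AE, and the article neither equalises it nor provides for recording it. An effect of the interval, of unknown size and direction, could be mixed with the environment effect in the immediate AE versus LE comparison. The conclusion rests on one necessary inference (AE participants must leave the water), on the absence of a stated LE wait, and on the plausible but undemonstrated assumption that performance changes over the minutes after exercise.

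The false-positive rates of about 10%, 16% and 37% describe assumed shifts only and should not be cited as the trial's error rate. The sample size is not affected. The change is worth making because it is cheap and because an interval that was not controlled or logged cannot be recovered after data collection.

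**What to change.** - Replace the rule of immediacy with one common interval from the end of the last set to the first post-test trial, long enough for AE participants to leave the pool and get ready. Have LE participants sit for the same time.
- Log the actual interval for every participant and report it by arm. Recording heart rate and perceived exertion at the start of the post-test would show whether the arms begin the test in a similar state. The logged interval can then be used in a sensitivity analysis of the immediate comparison.
- Give LE a five-minute seated period before exercise to match AE, so that the pre-test-to-exercise intervals also agree.

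The cost is a few minutes of waiting for LE participants, one logged time, and a slightly later post-test in LE. The analysis model and sample size need no change.

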
### Outcome measurement

A modified lean-and-release technique devised by Bolton and Mansour (2020) will be implemented on land to assess reactive balance immediately before (pre), after (post), and one week after (follow-up) the single bout intervention [25]. Lean-and-release techniques are commonly used to assess reactive balance in various older adult populations [35–37]. This modified lean-and-release technique additionally introduces cognitive factors (i.e., response inhibition and action selection), which are important in certain situations. For safety purposes, participants will wear a harness, which is secured to the ceiling to prevent them from falling in case they fail to recover balance. The participants will then stand with both feet hip-width apart on two separate, parallel force plates (type 9260AA, Kistler AG, Winterthur, Switzerland). A horizontal cable will be attached to the safety harness at the midthoracic level and the other end to the wall behind the participants by a magnet. To simulate a forward fall (trip) situation, the experimenter will instruct participants to lean forward into a support cable while keeping both feet in contact with the floor and to remain relaxed (Fig 2). This position will require dorsiflexion of the ankle, as the rest of the body remains aligned. The forward lean position for each participant, measured by the ankle joint angle, will be determined as the minimal lean angle where a change-of-support reaction (i.e., forward step) is necessary to recover balance upon cable release [38]. Then, the magnet will be deactivated to suddenly release the cable. There are two possible settings: 1) the leg block is placed in front of both legs, and a safety handle is uncovered; or 2) the leg block is removed, and the safety handle is covered. The leg block and handle cover will be controlled via computer-triggered, servo motors. The testing session will be comprised of three blocks: 1) REACH (grasping a safety handle using their right hand while maintaining both feet fixed), 2) STEP (stepping forward using any leg), and 3) RANDOM (random variations of STEP and REACH). To control vision during the third block, participants will wear liquid crystal goggles (Translucent Technologies Inc. Toronto, ON, Canada), that will be closed at the beginning of each trial and opened 400 ms before the cable is released. An experimenter will make careful note of the stepping leg used on each trial, and the participants will be free to step with either leg during testing. The timing of foot-off of the stepping foot will be recorded using the two parallel force plates. A force-sensitive resistor (B&L Engineering, Santa Ana, CA, USA) placed on the top surface of the safety handle and one large force plate in front of the two parallel force plates will be used to detect hand contact with the safety handle during REACH and foot contact during STEP, respectively. To control the predictability of the forthcoming reactions during the third block, the settings will be randomly changed between trials via the data collection program. After sufficient practice trials to familiarize the participants with the stepping and reaching actions, five trials each of the REACH and STEP will be completed, and ten actual trials of RANDOM, including five STEP and five REACH actions in random orders, will be completed. Outcome measurements at post and follow-up will include all randomized participants within the original groups regardless of any discontinuation or deviation from intervention protocols.

**Fig 2 pone.0275733.g002:**
[figure not shown]
Modified lean-and-release task. (A) Grasping a safety handle using right hand while maintaining both feet fixed. (B) Stepping forward using a preferred leg.

During the testing, the quality of the compensatory reactions will be scored using the Reactive Postural Control section of the mini‐BESTest [39,40]. The scores will be ranged from 0 to 2. The scoring criteria for the STEP task will be as follows: 0) no reactive step or falling; 1) more than one reactive step; and 2) one successful reactive step. For the REACH task, the criteria were modified as follows: 0) no grasp reaction or falling; 1) grasp reaction with one or more reactive steps; 2) successful grasp reaction without a reactive step. During the RANDOM block, the number of accurate responses will be recorded. The testing will be video-recorded and assessed by two experimenters, who are blinded to the allocation.

### Data processing and analysis

Force data in relation to the cable release will be extracted for further analysis to define the reaction time. Foot-off and foot contact will be defined as the time (ms) following the cable release at which the force under the stepping foot becomes less than and greater than 1% of the body weight, respectively [40]. Hand contact with the handle during REACH will be defined as the time following the cable release at which the force sensitive resistor detects a force.

For the RANDOM block, response accuracy, defined as the percentage of accurate responses, will be additionally calculated. To represent a composite measure of accuracy and speed of response, rapid response accuracy will be calculated using the ratio of response accuracy to the reaction time (%/ms), similar to the approach recently developed in a device measuring hand reactions (46). Foot-off and hand contact data will be used for the calculation.

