### Aquatic exercise

Exercises performed in an aquatic environment have been suggested as an effective alternative to exercises on dry land for people with a variety of clinical conditions as it offers a safer environment if one were to fall [14,15]. The effectiveness of aquatic exercise (AE) is fundamentally attributed to the physical properties of the water [14]. For example, the buoyancy of the water provides a supportive force and a reduction in joint loading. Viscous force and hydrostatic pressure enhance sensory and proprioceptive awareness, which may be beneficial to the postural control system [16]. In addition, the aquatic environment slows movements and enhances participants’ confidence level (i.e., decrease in fear of falling) by potentializing their ability to attempt movement outside their base of support [16]. Given these advantages of the aquatic environment, aquatic exercises have been widely implemented in the early stages of rehabilitation or used as a paradigm of aquatic cross-training [16,17]. Further, aquatic exercises are specifically advisable for those who cannot tolerate land-based exercises or strive for novel training stimuli.

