Hence, the current study aims to compare measures of reactive balance control after a single bout intervention on land and in chest-deep water. There have been several studies presenting greater enhancements in dry-land balance performance, specifically in static and proactive balance measures, such as Berg Balance Scale [26], 8-Foot Up and Go Test [27], and Functional Reach Test [28] following AE versus land exercise (LE) in healthy older adults. As none of the previous trials included any measures of reactive balance, the current study will specifically focus on improvements in reactive balance capacity after a single bout intervention. During aquatic exercises, water resistance produces overload during movements, and hydrostatic pressure constantly facilitates sensory awareness and motor functions. Further, the confidence level is augmented in the safer aquatic environment, which in turn increases variability in movement systems and maximizes neuromuscular adaptations. Thus, we hypothesize that participants in an AE group will present greater improvements (e.g., more accurate and rapid responses) during the reactive balance assessment compared to those in a LE group. The greater improvements will be demonstrated by faster response speed (i.e., shorter reaction time), greater accuracy alongside faster response speed (e.g., higher rapid response accuracy), and greater quality of response (e.g., higher mini-BESTest score). The Mini Balance Evaluation System Test (mini-BESTest) is a comprehensive clinical balance assessment, which evaluates four different balance control systems. This tool is commonly used by clinicians and practitioners and well known to be advisable to identify the disordered systems underlying balance control and design specific rehabilitation approaches in varied age and patient populations [29]. In this study, the second section (Reactive Postural Control) will be utilized to score the quality of compensatory balance responses.

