### Statistical analysis

Dependent variables included in the statistical analyses will be: 1) hand contact time during REACH; 2) foot-off time during STEP; 3) foot contact time during STEP; 4) rapid response accuracy during RANDOM; 5) mini-BESTest score of REACH; 6) mini-BESTest score of STEP; 7) mini-BESTest score of RADOM. There are two independent variables including the groups (AE vs. LE) and time (pre vs. post vs. follow-up).

The baseline differences in demographic data and all dependent variables between AE and LE groups will be analyzed using independent samples t-tests for data with a normal distribution and using the non-parametric Mann-Whitney U-test for data without normal distribution. On confirming the assumptions of the normal distribution (Kolmogorov–Smirnov test) and homogeneity of variances (Levene’s test), dependent variables will be compared using 2 (group: AE, LE) × 3 (time: pre, post, follow-up) repeated-measures (RA) analysis of variance (ANOVA) with group as a between-group factor and time as a within-group factor. If baseline differences of the dependent variables occur, baseline values will be included as covariates. If the assumptions are violated, Kruskal-Wallis one-way ANOVA will be used for nonparametric variables. In addition, post-hoc analyses will be conducted using Tukey post hoc test or Mann-Whitney U test. The meaningfulness of statistical differences will be reported using Cohen’s d effect sizes (ES) and confidence intervals (95%) for the parametrical variables and probability of superiority for dependent samples (PS_dep_) for the nonparametric variables [41]. Alpha will be set *a priori* at .05 for all statistical analyses. Missing data will be handled using multiple imputation, and all statistical analyses taking an intention-to-treat approach will be conducted with SPSS version 25 (SPSS Inc., Chicago, IL, USA).

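### A higher rapid response accuracy does not by itself show more accuracy with more speed, and the listed analyses include neither component from the RANDOM block

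*Protocol article*

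**What the plan says.** The hypothesis at the end of the Problem statement predicts three kinds of improvement in the aquatic group. One of them is "greater accuracy alongside faster response speed (e.g., higher rapid response accuracy". The other two are shorter reaction time and a higher mini-BESTest score.

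Data processing and analysis first gives the accuracy component: "For the RANDOM block, response accuracy, defined as the percentage of accurate responses, will be additionally calculated". It then forms the composite: "rapid response accuracy will be calculated using the ratio of response accuracy to the reaction time (%/ms". On the time component it says: "Foot-off and hand contact data will be used for the calculation".

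Outcome measurement describes three separate blocks, REACH, STEP and RANDOM. For the third it plans "ten actual trials of RANDOM, including five STEP and five REACH actions in random orders, will be completed".

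Statistical analysis fixes seven dependent variables. The first four are "1) hand contact time during REACH; 2) foot-off time during STEP; 3) foot contact time during STEP; 4) rapid response accuracy during RANDOM". The other three are mini-BESTest scores, one per block. RANDOM therefore contributes two variables: the ratio and a mini-BESTest score.

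**The concern.** The hypothesis is a joint claim: both accuracy and speed improve. A ratio of one to the other cannot carry that claim, because a gain in speed can outweigh a loss in accuracy. The usual safeguard is to look at the two components, but neither is on the list for RANDOM. The listed times belong to the REACH and STEP blocks.

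RANDOM is the block in which the required action changes unpredictably and vision opens only 400 ms before release. It is where response inhibition and action selection are tested. Half of the catches in the intervention (60 of 120) follow deceptive throws intended to train those same processes. If the ratio favoured one arm, the plan as written would allow a conclusion of better accuracy and better speed when the participants had become faster and less accurate.

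**Working it through.** The plan states no figure for this measure, so there is none to reproduce. The check is on how the ratio behaves.

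**Inputs from the protocol article.** Ratio R = A / T, with A in % and T in ms (Data processing and analysis). Ten RANDOM trials (Outcome measurement), so one error moves A by 10 percentage points. 22 participants per group (Sample size calculations).

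**Break-even, with no assumed times.** R rises when A_new / T_new > A_old / T_old, that is, when T_new / T_old < A_new / A_old. The proportional cut in time must exceed 1 − A_new / A_old.

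| Starting accuracy | One more error: cut must exceed | Two more errors: cut must exceed |
|---|---|---|
| 100% | 1 − 90/100 = 10.0% | 1 − 80/100 = 20.0% |
| 90% | 1 − 80/90 = 11.1% | 1 − 70/90 = 22.2% |
| 80% | 1 − 70/80 = 12.5% | 1 − 60/80 = 25.0% |

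The same inequality holds if the ratio is formed separately for STEP and REACH trials, so the point does not depend on which timing event is used.

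**Examples with assumed times** (the documents give none):
- 90% at 400 ms: 90/400 = 0.225 %/ms. 80% at 340 ms: 80/340 = 0.235. The less accurate pattern scores higher. Break-even is 400 × 80/90 = 356 ms.
- 100% at 450 ms: 100/450 = 0.222, which ranks below 90% at 400 ms.
- 90% at 360 ms and 80% at 320 ms: both 0.250. The ratio cannot tell them apart.

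**Simulation, as an illustration only.** 22 per group, ten trials each, reaction-time SD assumed to be 50 ms, two-sided t-test at .05 on a single time point (simpler than the planned repeated-measures ANOVA). A group at 80% and 320 ms has a mean ratio of 0.257, against 0.229 for a group at 90% and 400 ms. The less accurate group is declared significantly better in 44% of runs. At 300 ms the means are 0.275 and 0.229, and this happens in 80% of runs. With identical groups it happens in 2.4%, as expected in one direction.

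**What the list would reveal.** Set against the seven variables:
- RANDOM response accuracy is calculated but not listed.
- RANDOM foot-off and hand-contact times are needed to form the ratio but are not listed. If the REACH and STEP times were meant to include RANDOM trials of the same type, RANDOM times would be pooled with the others and still not analysed on their own. Accuracy would still be missing.
- The RANDOM mini-BESTest score is listed. A missing step or grasp scores 0, so some wrong responses lower it. However, an extra step after a correct step scores 1, and a fall scores 0 even if the right action was chosen. A lower score may therefore reflect wrong choices or poorer recovery.

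**The case against.** Six arguments can be made for leaving the plan alone.

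- **The mini-BESTest score covers it.** An arm making more wrong responses would tend to score worse on the RANDOM mini-BESTest, so the ratio does not stand unchecked. This stands in part. It is a real counter-check, but it does not isolate accuracy.
- **The data exist.** Accurate responses are recorded and the times must be available to form the ratio. This stands. A reader might infer that the trial is unable to show accuracy alongside speed. The documents do not support that: the limit lies in the listed analysis, not in the data.
- **The arms will not differ in strategy.** The Aquatic exercise section says that "the aquatic environment slows movements", and a reader might infer that the two arms will settle at different points on a speed-accuracy trade-off. The documents do not establish this. The sentence concerns movement in water, the test is on land, both arms receive the same task, and the Problem statement says that speed and accuracy will both be stressed. Any figure for such a shift needs an assumed trade-off curve, and the documents offer none.
- **The composite is declared and has a precedent.** It is openly called a composite, and a similar approach in a hand-reaction device is cited. That justifies reporting it. It does not make the joint reading in the hypothesis follow.
- **A statistical analysis plan may deal with it.** The article does more than stay silent: it fixes the list of dependent variables and ties the hypothesis to the ratio.
- **More outcomes mean more tests at .05, and ten trials measure accuracy coarsely.** This stands as a caution. It argues for supporting status and interval estimates. It also argues against a rule that one component must merely be no worse, because such a rule has no margin.

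**Conclusion.** The point holds for the planned analysis. The ratio rises whenever time falls proportionally more than accuracy, and the fixed list contains neither RANDOM component. A higher ratio therefore cannot support the joint claim in the hypothesis, and the RANDOM mini-BESTest score only partly fills the gap.

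The break-even cuts of 10.0%, 11.1% and 12.5% for one more error in ten rest only on the definition of the ratio and the ten trials. The example ratios and the 44% and 80% figures rest on assumed times, error rates and SD. They show that the misreading is possible, not how likely it is here. A reader might infer that a less accurate arm would be declared better. The documents do not support a prediction of that kind, since real reaction times and error rates are not given. The change is worth making before analysis because it alters what the trial may conclude from this outcome.

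**What to change.** In Statistical analysis, add three supporting outcomes:
- RANDOM response accuracy, as the number correct out of 10, in a binomial or logistic model that allows for repeated measures;
- RANDOM foot-off time, from STEP trials;
- RANDOM hand-contact time, from REACH trials.

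Report them beside the ratio with between-group estimates and 95% confidence intervals, and label them as supporting so that they are not read as further confirmatory tests.

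In the Problem statement, describe a higher ratio alone as a composite gain in accuracy and speed. Claim accuracy alongside speed only when the component estimates support it.

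The cost is a few lines of text and three more model fits on data already to be recorded. No new measurements or participants are needed. The downside is a few more reported outcomes. Accuracy will be estimated with limited precision: if both groups were at an assumed 90%, with 22 × 10 = 220 independent trials each, the 95% interval for the difference at one time point would be about ±1.96 × √(2 × 0.9 × 0.1 / 220) = ±5.6 percentage points, and wider if participants differ in ability. The interval should be shown for that reason, and a non-significant accuracy difference should not be read as no loss.
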